## **AIM(S) OF STUDY**

This study aims to evaluate the effectiveness of a digital intervention designed to support individuals with long COVID in managing their energy levels and preventing post-exertional malaise (PEM). By integrating a wearable activity tracker with a just-in-time adaptive intervention (JITAI) framework, the study seeks to explore how real-time alerts and retrospective activity analysis can help individuals regulate their daily activity levels. Ultimately, this research aims to determine whether such an intervention can enhance self-management strategies, reduce the frequency and severity of PEM episodes, and improve overall quality of life for people living with long COVID.

## **OBJECTIVES**

- To assess whether real-time activity alerts based on JITAI improve participants' ability to adhere to adaptive pacing strategies.

- To analyse retrospective activity data preceding PEM episodes to refine individual activity thresholds.
- To examine user experiences, feasibility, and adherence to the digital intervention for managing activity levels.
- To determine whether the intervention leads to a reduction in the frequency and severity of PEM episodes over time.

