## PARTICIPANT DEMOGRAPHICS

Supplementary table displaying participant characteristics of those who completed the study.

|              | Control (n=77)         | Intervention (n=84)    |
|--------------|------------------------|------------------------|
|              | Mean (95% CI)          | Mean (95% CI)          |
| Age (years)  | 47 (45-50)             | 45 (43-48)             |
| Gender (M/F) | 60 F (78%), 17 M (22%) | 66 F (79%), 18 M (21%) |

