## **STUDY DESIGN**

This study was designed as a pragmatic randomised controlled trial (RCT) to evaluate the effectiveness of an activity tracking and personalised just-in-time adaptive intervention (JITAI) for managing post-exertional malaise (PEM) in people with long COVID. A pragmatic RCT was chosen to assess the intervention in real-world conditions, with that findings are generalisable to routine clinical and self-management settings. Pragmatic trials consider diverse participant adherence, varied settings, and real-life constraints and this approach was intended to allow for a more comprehensive understanding of the intervention's feasibility, acceptability, and potential for real-world implementation.

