## **STUDY PROCEDURES**

#### *Recruitment of participants*

The following summaries will be presented for all participants screened for entry to the study, by identification or recruitment source and overall. For the purpose of recruitment, the

following summaries will be collected: 1) The number of participants screened, 2) The number of participants recruited, 3) Number and percentage of participants not recruited and the reasons for non-recruitment. Relevant summaries on recruitment, consent and data completeness during follow-up will be presented in a CONSORT flowchart. Reasons for withdrawal at different follow-up times will also be summarised by treatment arm.

Individuals expressing interest to trial information distributed via social media will be contacted via telephone or video conferencing for a briefing which will include screening for inclusion and exclusion criteria, a verbal overview of the study and an opportunity to ask questions. We will provide participants with an information sheet and re-contacted at least 7-days later to provide a further opportunity to ask questions and, if willing, enrol in the trial. Participants will provide written informed consent and then be allocated an enrolment number. Recruitment will be facilitated by our partner organisation, Long COVID Scotland, and involve promotion of the study via online social groups, social media, print media, a study website and meetings with Long COVID Scotland members. We will target people who have not been hospitalised following their COVID-19 infection. We expect to recruit 35 participants per month, and therefore should take 7-months.

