### *Statistical methods*

All analyses will be conducted using Jamovi version 2.3.21. Data will be tested for normal distribution and homogeneity of variance to confirm parametric assumptions are met. Data will be presented in text and tables as means and 95% confidence intervals (CI) unless otherwise stated. Because of randomisation, we did not undertake analysis of baseline equivalence, since the null hypothesis must be true and any differences due to chance . Only participants who completed follow-up testing were included in analysis (i.e. per protocol analysis). The effect of the energy management intervention on main and secondary outcomes will be examined using two-way mixed-model ANOVA with condition (intervention or control) as the between-subjects factor and time (pre- and post-intervention) as a within subjects' factor. Alpha level will be reported as exact p values and not described dichotomously as 'significant' or otherwise as recommended by the American Statistical Association . We will express effect sizes from the ANOVA as partial eta-squared ( $\eta^2p$ ), with values of 0.01, 0.06, and 0.14 interpreted as small, moderate, and large, respectively . For categorical data, (DSQ-PEM questions 6-10) we will use McNemar's Test for paired samples (pre- to post- intervention), or Chi squared test for between group effects (intervention vs. control).

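### The completers-only rule has no exception, so applied to the adherence objective it would leave out about a third of the intervention arm and probably overstate adherence

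*Protocol*

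**What the plan says.** Under Objectives, the third of four aims is "To examine user experiences, feasibility, and adherence to the digital intervention for managing activity levels". Study Design gives a related reason for choosing a pragmatic trial, namely to understand the intervention's "feasibility, acceptability, and potential for real-world implementation".

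Statistical methods contains the protocol's one rule on who is analysed: "Only participants who completed follow-up testing were included in analysis (i.e. per protocol analysis". The next sentence specifies the model: "The effect of the energy management intervention on main and secondary outcomes will be examined using two-way mixed-model ANOVA". No sentence says whether the completers rule stops at that model or also covers descriptive work such as adherence.

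Recruitment of participants plans some reporting on a wider base: "The following summaries will be presented for all participants screened for entry to the study, by identification or recruitment source and overall". It adds "Relevant summaries on recruitment, consent and data completeness during follow-up will be presented in a CONSORT flowchart" and "Reasons for withdrawal at different follow-up times will also be summarised by treatment arm".

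The supplementary Participant Demographics table is limited to completers ("Supplementary table displaying participant characteristics of those who completed the study"), with 77 in the control arm and 84 in the intervention arm.

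**The concern.** Adherence to a tracker and app is largely a question of who keeps using them and for how long. People who stop responding to the study are plausibly also those who stop wearing the tracker. An adherence figure taken only from people who answered the final questionnaires would then describe a favourable subset.

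This is a different problem from missing data in the efficacy comparison. The six-month questionnaire is needed to score the primary outcome, but it is not needed to measure tracker use. According to Study Implementation and the Intervention section, the server collects heart rate and steps in 1-minute epochs, counts minutes above the threshold each day and stores the processed results. For people who later drop out, the data up to the point of stopping were therefore collected, and using them needs no imputation.

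At stake is the claim about real-world use. Study Setting/Location presents the platform as scalable. A reader would judge that from the adherence figure, and it would come from the two-thirds who stayed.

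**Working it through.** **Inputs**
- Intervention completers: 84 (Participant Demographics). The table's own counts agree: 66 + 18 = 84. I assume that completing the study, as in the table, means the same as completing follow-up testing, as in the rule.
- Intervention participants randomised: 125, assumed. Sample size and statistical power gives 125 per group as the recruitment aim, and the note under Employment Status at Baseline treats 125 per group as the full total.
- Planned drop-out: 30% (Sample size and statistical power).
- Adherence rates: none are given. The values below are assumptions, used only to show a range.

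**Step 1: who the rule leaves out**
- Retained: 84/125 = 67.2%.
- Left out: 125 − 84 = 41, and 41/125 = 32.8%.
- At the plan's own 30% drop-out the number would be 0.30 × 125 = 37.5, so a loss of this order was foreseen when the rule was written.

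**Step 2: effect on an adherence figure**

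Let *a* be the share of days adhered to by completers and *b* the share for non-completers.
- All allocated = (84*a* + 41*b*)/125.
- Overstatement by the completers' figure = *a* − (84*a* + 41*b*)/125 = (41/125)(*a* − *b*) = 0.328(*a* − *b*).

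With *a* = 0.80 (assumed):

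| *b* (assumed) | All 125 | Overstatement (points) |
|---|---|---|
| 0 | 67.2/125 = 53.8% | 26.2 |
| 0.25 | 77.45/125 = 62.0% | 18.0 |
| 0.50 | 87.7/125 = 70.2% | 9.8 |
| 0.80 | 100/125 = 80.0% | 0 |

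The bias is upward whenever *b* is below *a*, and zero when they are equal.

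**Step 3: does other text exempt or cover adherence?**
- Statistical methods has no exemption. The completers sentence comes before the ANOVA sentence and is not tied to it.
- The demographics table shows a completers-only basis being used for a descriptive summary as well as for a model.
- The recruitment, data-completeness and withdrawal summaries cover everyone, but they do not report days of tracker use or days within the allowance.

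**Step 4: is there a measure of user experience?**

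The outcome list covers PEM, symptoms, quality of life, cognition, breathlessness, mental health, pain and self-efficacy. Neither App design and features nor Measurement tools has a usability, acceptability or experience item, and no interview is planned. The in-app issue log and call-back request in Study Implementation are a support function. Reasons for withdrawal come only from those who leave.

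**The case against.** The strongest reply is that the completers sentence was written for the outcome ANOVA. It sits directly before that model, and adherence is neither a main nor a secondary outcome. An adherence endpoint and its population are commonly left to the SAP, which is not at hand. This has force: that the rule governs adherence is an inference from unqualified wording, and the lack of a defined adherence endpoint is not raised here. The wording itself is still in the protocol and carries no limit, so the limit should be written in.

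Three stronger readings are tempting, and the documents do not support them.

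- *A reader might infer that feasibility as a whole is assessed only in completers and so conditions on retention.* Recruitment of participants contradicts this: screening, recruitment, data completeness and withdrawal by arm are all summarised outside the completer set.
- *A reader might infer that non-adherent people are removed by construction.* The rule selects on follow-up testing, not on tracker use. Someone can ignore every alert and answer the final questionnaire, or pace daily and miss it. The two probably correlate, but one does not define the other.
- *A reader might take a figure such as 10 to 26 points as the size of the bias.* That range assumes non-completers adhered on at most 50% of days against 80% in completers. If they adhered equally, the bias is zero.

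It is also fair to say that adherence while the device is in use is a legitimate description. It can stand beside the all-allocated figure.

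**Conclusion.** The point holds in limited form. Read as written, the completers rule would drop 41 of an assumed 125 intervention participants (32.8%) from any adherence summary. Adherence would be overstated by 0.328 times the gap between completers and non-completers. With 80% assumed in completers and 0 to 80% in non-completers, that is 26 to 0 percentage points. The share left out rests on the document's own counts plus the assumption of 125 randomised. The direction rests on non-completers having used the intervention less, which is likely but not shown. The size is unknown.

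Reported recruitment and retention are unaffected, and so is the primary efficacy result. The missing measure of user experience and acceptability is confirmed. It is a secondary mismatch between what is claimed and what is collected, and an SAP could not repair it because it cannot analyse data that were never gathered.

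**What to change.** 1. In Statistical methods, limit the completers sentence to the ANOVAs of main and secondary outcomes.
2. Summarise adherence from stored server data for everyone allocated to the intervention, over the full six months: days with tracker data, and days within the allowance in force on that day. Show days after stopping as non-use, so that a day without data never counts as a day within the allowance.
3. Give the completers' figure, or the figure while the device was in use, as a secondary line.
4. Report how many participants have no data because they asked for deletion. Ethical Considerations provides for deletion five days after such a request, so some who dropped out may have no record left.
5. Use alert opening as a metric only if it was logged. Messaging describes what happens when an alert is tapped, but does not say that taps are recorded.
6. Remove user experiences from Objectives and acceptability from Study Design, or state the data source. A new exit question is probably too late, since the supplementary tables and figures already report completers and PEM days.

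The cost is a few words of protocol text and one descriptive table from data already collected. The downside is a less favourable adherence figure.

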## **HYPOTHESIS**

### *Primary Hypothesis*

**H0:** An activity tracking and personalised JITAI will not reduce symptoms of post-exertional malaise (PEM) in people with long COVID compared to usual care six months after randomisation.

**Ha:** There will be differences in symptoms of PEM in people with long COVID compared to a usual care group six months after randomisation in an activity tracking and personalised JITAI.

### *Secondary Hypotheses*

#### □ **Quality of Life**

- **H0:** An activity tracking and personalised JITAI will not improve quality of life in people with long COVID compared to usual care six months after randomisation.
- **Ha:** An activity tracking and personalised JITAI will improve quality of life in people with long COVID compared to usual care six months after randomisation.

#### □ **Anxiety and Depression**

- **H0:** An activity tracking and JITAI will not improve anxiety and depression in people with long COVID compared to usual care six months after randomisation.
- **Ha:** An activity tracking and personalised JITAI will improve anxiety and depression in people with long COVID compared to usual care six months after randomisation.

#### □ **Breathlessness**

- **H0:** An activity tracking and personalised JITAI will not improve breathlessness in people with long COVID compared to usual care six months after randomisation.

- **Ha:** An activity tracking and JITAI will improve breathlessness in people with long COVID compared to usual care six months after randomisation.

#### □ **Cognitive Function**

- **Ho:** An activity tracking and JITAI will not improve cognitive function in people with long COVID compared to usual care six months after randomisation.
- **Ha:** An activity tracking and personalised JITAI will improve cognitive function in people with long COVID compared to usual care six months after randomisation.

## **STUDY DESIGN**

This study was designed as a pragmatic randomised controlled trial (RCT) to evaluate the effectiveness of an activity tracking and personalised just-in-time adaptive intervention (JITAI) for managing post-exertional malaise (PEM) in people with long COVID. A pragmatic RCT was chosen to assess the intervention in real-world conditions, with that findings are generalisable to routine clinical and self-management settings. Pragmatic trials consider diverse participant adherence, varied settings, and real-life constraints and this approach was intended to allow for a more comprehensive understanding of the intervention's feasibility, acceptability, and potential for real-world implementation.

## **STUDY SETTING/LOCATION**

The study was conducted remotely within the UK, with participants undergoing the intervention or control conditions in their own homes and during their day-to-day activities. While the study was coordinated from The University of the West of Scotland, all aspects of participant engagement, data collection, and intervention delivery were designed to integrate into participants' everyday lives. This facilitated the evaluation of a scalable digital support platform that could be implemented without requiring in-person contact. Additionally, conducting the study in this way allowed for a meaningful evaluation within the context of a pandemic, where ongoing social distancing measures limited access to traditional healthcare and in-person research participation.

## **STUDY POPULATION**

The study population consists of individuals with long COVID who were not hospitalised during their initial COVID-19 infection and are managing their symptoms independently while

living in the community. To ensure broad representation, recruitment was conducted through support groups and community networks. This approach aimed to reflect the known demographic distribution of long COVID in the general population, considering factors such as the proportion of males and females, age distribution, and the prevalence of comorbidities within the non-hospitalised long COVID group.

## **ELIGIBILITY CRITERIA**

### *Inclusion criteria*

Participants had to meet the following criteria to be eligible for the study:

1. Adults (18 years or older) reporting persistent symptoms lasting at least 8 weeks after initial COVID-19 infection, which interfere with day-to-day activities and who were not hospitalised in the acute infection phase.
2. Individuals recovering at home rather than in a hospital or clinical setting.
3. Access to a compatible mobile device:
  - Android phone (SDK16 or higher) **or** iPhone (iOS version 10 or higher).

### *Exclusion criteria*

Individuals were excluded from the study if they met any of the following criteria:

1. Currently receiving ongoing care for long COVID through primary or secondary healthcare services.
2. Prior diagnosis of a comorbidity with similar symptoms (e.g., ME/CFS).
3. Currently receiving a therapy known to cause symptom exacerbations.
4. Participation in another long COVID-focused intervention at the time of enrolment.
5. Impaired cognitive function that compromises comprehension of study information or the ability to engage with the intervention.
6. Insufficient English language proficiency for effective communication via study messaging.
7. No access to a mobile phone, preventing engagement with the intervention.

## **STUDY OUTCOMES**

Primary and secondary outcomes were designed to meet the domains of the Long COVID core outcome sets (LC-COS). At the time of development, the LC-COS had not been

finalised. However, the initial Delphi survey had been completed. Consequently, the instruments included in the app were selected to reflect each of the major domains that emerged from the Delphi process The development team were also mindful to select instruments that were both valid yet minimised participant burden.

#### *Primary Outcome*

The primary outcome of the study is post-exertional malaise (PEM), assessed in terms of its frequency, severity, and duration. This domain captures the impact of activity on symptom exacerbation, including the persistence of symptoms following exertion.

#### *Secondary Outcome(s)*

Secondary outcomes include a range of physical, cognitive, and psychosocial health domains relevant to long COVID. These include:

- Overall symptom burden, including self-reported symptom frequency, persistence, and new COVID-19 infections.
- Quality of life, capturing physical, mental, and functional well-being.
- Neurological and cognitive function, including assessments of memory, attention, and nervous system symptoms.
- Respiratory function, specifically breathlessness and its impact on daily activities.
- Mental health, assessing anxiety and depression.
- Pain, measured through self-reported intensity and impact.
- Self-management and self-efficacy, evaluating participants' confidence in managing their condition.

These outcome domains have been selected to reflect the LC-COS core outcome set, ensuring that the study captures key aspects of long COVID that affect daily life.

## **STUDY PROCEDURES**

#### *Recruitment of participants*

The following summaries will be presented for all participants screened for entry to the study, by identification or recruitment source and overall. For the purpose of recruitment, the

following summaries will be collected: 1) The number of participants screened, 2) The number of participants recruited, 3) Number and percentage of participants not recruited and the reasons for non-recruitment. Relevant summaries on recruitment, consent and data completeness during follow-up will be presented in a CONSORT flowchart. Reasons for withdrawal at different follow-up times will also be summarised by treatment arm.

Individuals expressing interest to trial information distributed via social media will be contacted via telephone or video conferencing for a briefing which will include screening for inclusion and exclusion criteria, a verbal overview of the study and an opportunity to ask questions. We will provide participants with an information sheet and re-contacted at least 7-days later to provide a further opportunity to ask questions and, if willing, enrol in the trial. Participants will provide written informed consent and then be allocated an enrolment number. Recruitment will be facilitated by our partner organisation, Long COVID Scotland, and involve promotion of the study via online social groups, social media, print media, a study website and meetings with Long COVID Scotland members. We will target people who have not been hospitalised following their COVID-19 infection. We expect to recruit 35 participants per month, and therefore should take 7-months.

### *Randomisation*

Participants will be randomised to one of the two trial arms using 1:1 allocation ratio. Randomisation will be performed by a web-based online randomisation system (Study Randomizer). We will randomise participants remotely and participant blinding is impossible given the nature of the intervention.

### *Study procedure*

The intervention will be a randomised controlled trial (RCT) to determine if adaptive pacing (AP) using activity tracking and just-in-time support messages can improve symptom management of people with long-COVID. The trial will compare the symptom management of people allocated to usual care versus those receiving the intervention. The intervention will be provided via a bespoke support platform incorporating a wearable activity tracker (Fitbit Charge 5, Fitbit, USA), a data processing server, and a cross-platform (iOS and Android) mobile app (PaceMe). Participants will be recruited via online adverts and through long-COVID support groups. Those interested in taking part will undergo a screening interview for

eligibility and were subsequently randomised by a third party (studyrandomizer.com) into intervention or control arms of the trial balanced for gender.

